### Exploratory Agency Follow-Up

We will conduct a set of intensive follow-up agency interviews with community first responder organizations with whom we have established active communication. We will prioritize qualitative recruitment of organizations and agencies that did not agree to be recruited after establishing correspondence because the elicitation of barriers to participation in the *PulsePoint-OD* program may be most informative when carried out with those who did not participate. This procedure will be similar in principle to, but more extensive than, our brief study of clinical providers who dropped out from a continuing medical education program [71]. However, we will not exclude participating agencies from the qualitative component of the project; instead, we will continue data collection until we have reached a point of theoretical inductive saturation, when new conversations and data no longer seem to add to our understanding of the topic [72]. Interviews will be guided by a semistructured interview guide to be developed during the agency recruitment process and will be coded using the general inductive approach to qualitative analysis [73], which does not make a priori assumptions about the data and allows themes to emerge organically based on repeated readings of the data.

### Ethical Considerations

Ethics approval for the proposed work was determined to fall into 2 separate categories. Agency-level recruitment and interaction were determined not to constitute human participant research (Indiana University Institutional Review Board: 20218). The collection of information from layperson responders was approved under an expedited procedure (Indiana University Institutional Review Board: 20219). Data from layperson responders will be anonymous (no identifiers will be collected). Participation in the intensive follow-up agency interviews will be incentivized with an honorarium (US $500) to the organization to encourage participation.

## Results

At the time of protocol submission, we had not engaged in any data collection or participant recruitment. This research was funded beginning September 14, 2023, by the National Institute on Drug Abuse of the National Institutes of Health (R34DA058162).

## Discussion

### Summary

The primary goal of this study is to understand the feasibility of recruiting current *PulsePoint* communities and layperson responders to complete overdose and naloxone training and to carry naloxone. Our hypotheses are intended to determine whether a specific type of correspondence targeting anticipated misunderstandings around opioid overdose and naloxone performs better when recruiting agencies and laypersons than standard messaging and whether active recruitment of laypersons using either message type performs better than the control.

At the same time, a separate consideration—regardless of the results of null hypothesis significance testing—is an overall sense of recruitment feasibility (eg, data on agency and responder uptake). Successful completion of this study is anticipated to improve the level of naloxone coverage in the United States, which remains insufficient [29]. We are also interested in examining elements that did and did not work and how we would ideally structure a similar recruitment process for a larger, outcomes-focused study (eg, comparing fatal overdose ratios in communities). Our exploratory discussions with agencies will be important to facilitate a better understanding of the mechanisms through which the proposed recruitment procedures did (or did not) work as intended.

Where possible, we have tried to control for anticipated limitations at the stage of study design. Owing to the nature of this real-world study, we still anticipate some limitations in the interpretation of the results. In particular, the degree to which agencies will agree to participate in arm 3 is uncertain because participation does not directly benefit those communities (unlike arms 1 and 2). This would not affect H1 (which only includes arms 1 and 2) but might affect the statistical power of H2. We expect that additional limitations may be uncovered in the process of conducting the study, and we plan to transparently note, and where possible mitigate, all such limitations, providing a comprehensive description of this information in subsequent documentation of the study.

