**Methods:**

This will be a 3-arm parallel-group randomized controlled trial. We will randomly select 180 first responder agencies from the population of agencies contracting with the PulsePoint Foundation. The 3 study arms will include a standard recruitment arm, a misperception-correction recruitment arm, and a control arm (1:1:1 allocation, with random allocation stratified by zip code designation [rural or nonrural]). We will study agency recruitment and, among the agencies we successfully recruit, responder certification of receiving overdose and naloxone education, carrying naloxone, or both. Hypothesis 1 contrasts agency recruitment success between arms 1 and 2, and hypothesis 2 contrasts the ratios of layperson certification across all 3 arms. The primary analyses will be a logistic regression comparing the recruitment rates among the arms, adjusting for rural or nonrural zip code designation.

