#### Hypotheses

We will test the following hypotheses:

H1: more first responder agencies will be successfully recruited by arm 2 than by arm 1.H2: more layperson responders will report engaging with OEND programming in arm 2 than in arms 1 or 3 and in arm 1 than in arm 3.

As an exploratory follow-up, we will conduct incentivized qualitative follow-up interviews with agencies to better understand barriers to participation and how to improve uptake feasibility.

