### H1: First Responder Agencies

#### Parameters

The following parameters describe the interrelationships between communities and agencies for this study:

The PulsePoint Foundation reports that approximately 4800 communities currently use the *PulsePoint* app.Community participation and the use of the *PulsePoint* app are supported by agency contract holders; there are >755 such contracts in place.A contract-holding agency can serve multiple communities (eg, a county 911 office can offer *PulsePoint* to 9 different communities in the county, such as townships). An agency can also serve a single community (eg, a city fire department can offer *PulsePoint* to that city only).Any number of *additional* first responder agencies (eg, fire or police departments, emergency medical services, 911 call centers, or related entities) can contribute to a community or cluster of communities covered by a single *PulsePoint* contract, but these agencies are not contract holders.

When *PulsePoint* is introduced to a community for layperson use, the PulsePoint Foundation neither directly recruits nor interfaces with individual lay responders. Instead, the contracted first responder agencies conduct local recruitment and have the ability to send *push messages* (app-driven notices and messages) to users. Therefore, to integrate OEND into the *PulsePoint* network (eg, *PulsePoint-OD*) and for our study team to directly contact the subset of active users within each study community, it is necessary that the contract-holding first responder agencies in each community agree to participate. This first phase of the overall study (and the first hypothesis) pertains to agency-level recruitment.

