#### H1: Sample Size, Power, and Analysis

Although we plan for 180 agencies to compose the total sample size, only 120 (66.7%) will be allocated to arms 1 (n=60) and 2 (n=60), meaning that the sample size for this hypothesis is 120. With 60 agencies in each arm, we will have 80% power to detect significant differences (2-tailed α=.05) between arms 1 and 2 in the proportions of agencies that are successfully recruited if the difference in proportions is at least 0.25 (eg, 18/60, 30% recruited in arm 1 vs 33/60, 55% recruited in arm 2). The primary analysis will be conducted using logistic regression, comparing the recruitment rate between the arms. We will report exact P values and commit to a cautious interpretation of the findings, avoiding overreliance on P values as the single arbiter of meaning [64]. We do not expect any missing data in the outcome variable because the nature of its computation is such that missing data mean that either *A*=*0* or *R*=*0* and are therefore built into outcome variable *M*.

The primary study outcome (*M*) will be tested separately for the periods 6 and 12 months after initial recruitment correspondence. Analysis covariates are planned to include, but may not be limited to, community rurality and the community’s percentage vote share for the Republican candidate in the 2020 presidential election (available for 2523 US counties and separable by zip code [65]), given that political orientation was 1 of 2 strongly predictive variables in our regression model examining misperceptions of OEND [39].

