### H2: Layperson Responders

#### Overview

Layperson responders who are part of the *PulsePoint* system register with a local first responder agency using their smartphone. Most layperson responders (eg, those who are not also off-duty first responders themselves) are only alerted to incidents in public spaces. No identifying information is collected from these users except the unique ID of the device.

The first responder agency in each community that manages the *PulsePoint* subscription can only determine the number of active users and, broadly, the type of smartphone being used (eg, Android smartphone or iPhone). Each time a first responder agency sends out a push notification, it is provided with an exact count of the number of unique devices, separated by type, that were active in the system and reached by the message.

It is important to note that we will have a count of unique active devices but not necessarily a count of unique active users (eg, it is unlikely but possible that someone will install the app on 2 different mobile phones at the same time). In correspondence with the PulsePoint Foundation, it is likely that the count of unique active devices serves as a very close approximation of unique active users. Furthermore, by virtue of randomization, the distribution of any unmeasured anomalies related to user-device mismatches should be evenly distributed across the arms.

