#### Conceptualizing Recruitment for Layperson Responders

Currently, for a *PulsePoint* user to be officially recruited as a CPR responder and to be sent notifications regarding unconscious and unresponsive persons in public places, they need to affirmatively indicate that they are trained in CPR *and* are “willing to assist in case of an emergency.” Individuals who so verify are sent push alerts and auditory alert tones, regardless of whether the app is open, whenever there is an unresponsive and unconscious person within a specific radius of their mobile phone (the radius is specified by the first responder agency for that community) [66].

For the purposes of this study, a layperson responder will be considered to have been recruited for *PulsePoint-OD* if they certify that they have received training on overdose and naloxone and that they currently carry naloxone on their person (both outcomes are of interest, which we describe later in the *Outcome Variables and Measurement* section). Once an MOU is in place with a first responder agency, it will send out a customized baseline push message to all active users containing a link to a landing page. This page will contain brief introductory text explaining the importance of recognizing an overdose when responding to unconscious persons and the efficacy of naloxone, as well as 2 questions asking them to indicate, by pressing radio buttons, whether they have received training on recognizing an overdose and administering naloxone and whether they currently carry naloxone on their person. Additional push messages encouraging users to respond to the certification questions will be sent twice within the month to maximize the number of participants providing baseline data. A user’s responses to these questions will not change their status within the app or the behavior of the app because all users are already alerted to unresponsive or unconscious persons who may have experienced an overdose. This certification procedure will be repeated twice (6 months and 12 months after the baseline certification requests are sent). These messages will emphasize that even users who have previously provided such information should do so again.

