#### Sample Size, Power, and Analysis

Our power analysis for H2 depends on the number of communities that agree to participate during the agency recruitment conducted as part of testing H1. To compare the average proportions of users who certify that they have received overdose education and personally carry naloxone, we sought 80% power to detect significant differences (2-tailed α=.05) among the 3 arms across 3 time points. Assuming a correlation of 0.5 in responses over time, we expect that we will be able to detect a medium effect size ranging from *f*=0.21 (if 50, 83% of the 60 communities participate in each arm on average) to *f*=0.34 (if 20, 33% of the 60 communities participate in each arm on average).

Our primary analyses will be metrics *X* and *Y* (as described previously), which will be analyzed separately. The primary analyses will be conducted using generalized linear mixed models, adjusting the *df* for the number of agencies. As with H1, we will report exact P values and commit to a cautious interpretation of the findings, avoiding overreliance on P values as the single arbiter of meaning [64]. In addition, as in the case of H1, we do not expect any missing data in the outcome variable because the nature of its computation is such that missing data mean that either *N*=*0* or *C*=*0* and are therefore built into outcome variables *X* and *Y*. Study covariates will include but may not be limited to variable *Z* to control for the conversion of push messages to clicks.

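### H2 compares only agencies that agreed to join after randomisation; the protocol names lost power as the consequence but not selection bias, and does not fix a baseline-referenced contrast

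*Protocol article*

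**What the plan says.** The abstract's Methods restrict H2 to outcomes "among the agencies we successfully recruit, responder certification of receiving overdose and naloxone education" and related certification. The H1 Parameters section explains why: before any user can be contacted, "it is necessary that the contract-holding first responder agencies in each community agree to participate". H2 data start later still: "Once an MOU is in place with a first responder agency, it will send out a customized baseline push message to all active users" (Conceptualizing Recruitment for Layperson Responders).

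Agreement depends on arm. H1 is that "more first responder agencies will be successfully recruited by arm 2 than by arm 1", and its power example is "18/60, 30% recruited in arm 1 vs 33/60, 55% recruited in arm 2". Arm 3 agencies are asked only to put the certification questions to their users at three time points, with no campaign.

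On consequences, the H2 sample size section says "Our power analysis for H2 depends on the number of communities that agree to participate during the agency recruitment" and goes on to detectable effects of f=0.21 with 50 agencies per arm and f=0.34 with 20. The Discussion calls agreement in arm 3 uncertain, because those communities gain nothing directly, and concludes: "This would not affect H1 (which only includes arms 1 and 2) but might affect the statistical power of H2". The H2 analysis is a generalized linear mixed model for X and for Y over three time points. Z, the click ratio, is the only covariate named, in a list left open. Rurality and vote share are named for H1.

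**The concern.** Joining happens after randomisation and before every H2 measurement, and the arm-specific recruitment is intended to change it. Randomisation makes the 60 agencies per arm comparable. It does not make the subsets that join comparable. If arm 2's message persuades agencies that the standard message would have lost, the arm 2 joiners are a different mix from the arm 1 joiners. Arm 3's smaller request, without direct benefit, may select differently again.

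A difference in X or Y could then reflect which agencies joined rather than what their users were sent. This matters because the abstract's Conclusions say the best-performing approach goes into the next phase. The protocol sees the uneven agreement but describes only its effect on numbers.

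**Working it through.** **1. The plan's own figures.** H1: 60 per arm, 30% vs 55%, two-sided α=0.05 gives power 79.9% (stated 80%). H2: take the between-arm effect in a repeated-measures ANOVA with 3 arms, m=3 time points and ρ=0.5. The test is F with (2, N−3) df and noncentrality λ = f²·N·m/(1+(m−1)ρ) = f²·1.5N. Solving for 80% power:

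- N=150: f=0.209 (stated 0.21).
- N=60: f=0.336 (stated 0.34).

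An arm-by-time effect would give 0.116 and 0.186, which do not match. The stated figures therefore belong to an arm difference averaged over all three time points, baseline included. That contrast gives no protection against a stable difference between joiners.

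**2. Illustration under no message effect.** From the document: 60 agencies per arm, 30% and 55% agreement (an example of a detectable difference, not a forecast), ρ=0.5. Assumed, not in the document: 15% agreement in arm 3; the most willing agencies join; and r, the correlation between willingness and the agency's stable certification level. Joiners number 18, 33 and 9.

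Mean willingness of the top fraction p of a standard normal is φ(z)/p, where z is the cut-off: 1.159 (30%), 0.720 (55%), 1.554 (15%). Multiplying by r gives the shift in the stable level:

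| r | arm 1 | arm 2 | arm 3 | 2 − 1 | 2 − 3 |
|---|---|---|---|---|---|
| 0.3 | 0.348 | 0.216 | 0.466 | −0.13 | −0.25 |
| 0.5 | 0.579 | 0.360 | 0.777 | −0.22 | −0.42 |

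With ρ=0.5 the stable part carries half the variance of a single ratio, so the shift in ratio units is √0.5 times these values. The mean of three time points has variance (1+2·0.5)/3 = 2/3.

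For the 3-arm test, λ = Σnᵢ(μᵢ−μ̄)²/(2/3), with 2 and 57 df:

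- r=0: λ=0, rejection 5%.
- r=0.3: μ = 0.246, 0.153, 0.330; λ=0.39; rejection 8%.
- r=0.5: μ = 0.410, 0.254, 0.550; λ=1.08; rejection 14%.

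Simulation with random numbers of joiners (3,000 runs per setting) gives about 5%, 7% and 15%.

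**3. Unequal uptake is neither sufficient nor necessary.** At r=0, uneven uptake leaves rejection at about 5%. With equal 33% uptake, but willingness related to the outcome in arms 1 and 3 only, the simulation rejects 13% (r=0.3) and 31% (r=0.5). Counts of joining agencies therefore cannot settle the question.

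**4. What a baseline reference does.** In this model the ratio at time t is √0.5·U + √0.5·eₜ, where U is the agency's stable level. Subtracting the D=0 value removes U and with it the selection shift. If willing agencies also respond more to messages, that part remains.

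**The case against.** Several points on the other side stand.

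- **Different kinds of agencies.** A reader might infer that the protocol expects this. It does not say so. H1 predicts how many agree, and arm 3 agreement is called uncertain, not low. Arm 3 also asks less, so its uptake could be higher. That different agencies join is an inference from the different messages and requests.
- **Direction.** A reader might infer that the arm with least uptake is the most favourably selected, so that bias runs against arm 2. That needs one readiness ranking to apply in all arms, which the documents do not support.
- **Size.** If r is taken as the correlation with each observed ratio and single pairs are tested, the rejection rate for arm 2 vs arm 3 reaches 27% at r=0.5. That is the far end of assumed inputs and not the 3-arm comparison.
- **Appeal to randomisation.** The H2 Overview says "by virtue of randomization, the distribution of any unmeasured anomalies related to user-device mismatches should be evenly distributed across the arms". This concerns people with two phones. It claims no balance in agency readiness and needs no change.
- **Baseline is in the design.** X and Y are measured at D=0, so a mixed model over three time points could carry an arm-by-time contrast. But the protocol does not name it, and the power figures match a different contrast.
- **Setting.** This is a feasibility trial in which agency consent is unavoidable. Covariates are left open, detailed adjustment may sit in an analysis plan not shown, and cautious interpretation is promised.

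These points limit the claim. They do not answer it, because the Discussion itself takes up uneven agreement and states its consequence incompletely.

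**Conclusion.** The concern holds in conditional form. Allocation is randomised; the H2 comparison among joiners is not protected by it if willingness to join is related to X or Y and the arms attract different agencies. Naming power alone is then incomplete. Direction and size cannot be derived from the documents. The 7% to 15% rejection rate under no effect rests on the assumed correlation of 0.3 to 0.5, 15% uptake in arm 3, the 30%/55% example and a test averaged over time. The plan's power figures are arithmetically right; they answer only how many agencies join.

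A reader might also infer that H2 should be rescued by analysing all 60 agencies per arm with non-joiners scored X=Y=0. That would not test the layperson messages. Non-joiners have no T, and the zeros create an arm difference at D=0, before any monthly recruitment message, whenever uptake differs and baseline certification is not zero. It would largely repeat H1.

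**What to change.** 1. In the H2 Sample Size, Power, and Analysis section, make the primary contrast the arm difference in X and in Y at 6 and 12 months relative to the agency's own D=0 value (arm-by-time or baseline-adjusted). Adjust for rurality, which is the randomisation stratum, and for vote share, already planned for H1.
2. Compare joining agencies across arms on baseline X and Y, rurality, vote share and existing naloxone distribution, which the After Recruitment section already collects. Describe H2 as a comparison among self-selected agencies.
3. In the Discussion, say that differential agreement may bias H2 as well as reduce its power.
4. Optionally, add the all-randomised analysis with non-joiners counted as zero certifications, as a secondary measure of total strategy yield only.

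The cost is text and a changed model term; the data are already planned, and none had been collected at submission. Two limits should be stated. Baseline adjustment does not remove differences in responsiveness. D=0 is itself measured after arm-specific agency recruitment, and the arm 3 landing page is described as carrying no additional information. The detectable effect must be restated for the chosen contrast: the arm-by-time values of 0.116 and 0.186 are on a different scale and cannot be read against 0.21 and 0.34 as a gain.

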### Conclusions

If we successfully recruit agencies and laypersons and thereby facilitate training around overdose and naloxone and increase the numbers of layperson responders carrying naloxone, the next step will be to conduct a larger study examining opioid-involved overdose reversals using these procedures. This is predicated on current evidence for OEND, which allows us to hypothesize that our successful mobilization of layperson responders might reduce the prevalence of opioid-involved overdose [12-16], a theory that we will then prospectively test.

